**Fig. 2 Fig2:**
[figure not shown]
Screenshot of the SRTT software used in this study

The task includes 10 practice trials followed by 80 experiment trials, collectively lasting no more than 10 min for each participant. The interstimulus interval (measured in milliseconds, refers to the duration between a response and the subsequent appearance of a cross) will be randomly set within the range of 1000–3000 ms. The computer program will record the response time and the interstimulus interval for each trial [33].

##### Electroencephalogram (EEG)

A wireless multichannel EEG acquisition system will be used (32-channel ZhenTech, China) to record the participants’ brain activity while performing SSRT (Fig. 3). The sampling rate will be set at 1000 Hz, and a notch filter (50 Hz) will be applied to filter out the powerline interference.

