**Methods:**

This study employs a double-blind, sham-controlled, randomized controlled trial design with a 2-week intervention period. Both participants and outcome assessors will remain unaware of treatment allocation throughout the study. Thirty-nine stroke patients will be recruited and randomized into three distinct groups, including the sham tACS group (SS group), the single-target tACS group (ST group), and the multi-target tACS group (MT group), at a 1:1:1 ratio. The primary outcomes are series reaction time tests (SRTTs) combined with electroencephalograms (EEGs). The secondary outcomes include motor evoked potential (MEP), central motor conduction time (CMCT), short interval intracortical inhibition (SICI), intracortical facilitation (ICF), magnetic resonance imaging (MRI), Box and Block Test (BBT), and blood sample RNA sequencing. The tACS interventions for all three groups will be administered over a 2-week period, with outcome assessments conducted at baseline (T0) and 1 day (T1), 7 days (T2), and 14 days (T3) of the intervention phase.

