## Introduction

### Background and rationale {6a}

Motor learning refers to the acquisition and solidification of a new motor skill, which plays an important role in rehabilitation activities [1]. The process of motor learning involves multiple brain regions, accompanied by changes in synaptic plasticity that can improve motor dysfunction caused by neurological damage, such as stroke [2]. In fact, the reacquisition of motor skills via motor learning holds the utmost significance in the recovery process of poststroke hemiparesis [3]. Therefore, the quest for efficacious tools and treatments to enhance motor learning after stroke becomes imperative.

Neural oscillations are rhythmic electric processes of neuron groups in the central nervous system that include five frequency bands: delta (δ, < 4 Hz), theta (θ, 4–7 Hz), alpha (α, 8–12 Hz), beta (β, 13–30 Hz), and gamma (γ, 30–100 Hz). In particular, γ oscillations are considered to emerge by activation of reciprocally connected excitatory pyramidal neurons and inhibitory interneurons and control the connectivity between different brain regions, which is crucial for perception, movement, memory, and emotion [4]. Studies show that γ oscillations, approximately 40 Hz, have been recorded during movement preparation during both externally triggered and self-paced hand movements [5], which means that γ oscillations are always present during movement onset and execution [6] and reflect the integration of visual, proprioceptive, and somatosensory information with ongoing motor activity.

Recent studies have shown that noninvasive brain stimulation (NIBS) techniques, such as transcranial alternating current stimulation (tACS), have emerged as potent tools to induce neural oscillations in the brain network. tACS can improve motor performance differentially by the injection of sinusoidal currents to modulate cortical excitability and brain electrical activity [7]. Compared to transcranial magnetic stimulation (TMS), tACS devices are inexpensive and convenient to use and have smaller electrode pads that can achieve multi-target stimulation in the brain. Furthermore, tACS can set different stimulation frequencies to induce different neural oscillation bands compared to transcranial direct current stimulation (tDCS).

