## Statistical methods

### Statistical methods for primary and secondary outcomes {20a}

Statistical analysis will be performed using IBM SPSS Statistics 25 (http://www.spss.com.hk). Independent statisticians who remain blinded to the grouping will use an intention-to-treat (ITT) analysis approach to scrutinize the study results. In the case of missing data, the last observation value will be used for interpolation. Continuous variables conforming to a normal distribution will be described as the mean ± SD, while nonnormal distributions will be presented as medians, and the categorical variables will be described using frequency counts. The two-way variance with repeated measures will be performed for continuous variables that meet the assumptions of a normal distribution and homogeneity of variance, while the Wilcoxon test will be used if not. A chi-square test will be performed for categorical variables. The comparison between the three groups will use a two-tailed multivariate analysis of variance. When the *P* value was less than 0.05, the results were statistically significant. The post hoc comparisons will be performed by the Bonferroni correction for multiple comparisons if necessary.

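### EEG is a primary outcome with no named variable, and the P < 0.05 rule controls neither the choice among EEG measures nor the pair SRTT and EEG

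*Protocol article*

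**What the plan says.** The Abstract (Methods) states: "The primary outcomes are series reaction time tests (SRTTs) combined with electroencephalograms (EEGs"). The section Outcomes {12} repeats this by placing EEG under the Primary outcomes heading. What follows there is acquisition only: "A wireless multichannel EEG acquisition system will be used (32-channel ZhenTech, China"), then "The sampling rate will be set at 1000 Hz, and a notch filter (50 Hz) will be applied to filter out the powerline interference", then instructions to participants about movement, swallowing and phones.

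The Background lists neural oscillations "in the central nervous system that include five frequency bands" and stresses gamma activity near 40 Hz, the frequency used for stimulation. No section turns this into an EEG endpoint.

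Statistical methods {20a} plans a repeated-measures analysis of variance for continuous variables. It adds: "The comparison between the three groups will use a two-tailed multivariate analysis of variance". The decision rule is: "When the *P* value was less than 0.05, the results were statistically significant". A Bonferroni correction is foreseen for post hoc comparisons, and only conditionally. The section on additional analyses {20b} plans none.

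**The concern.** A primary outcome is a variable, not a recording. Thirty-two channels of EEG at four assessment times can yield very many variables (power, phase or connectivity, by band, site and time), and the article does not say which one carries the primary claim. The stated error control does not reach that choice. Nor is there a rule for SRTT and EEG together: the article does not say whether one must succeed or both.

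At stake is what a significant EEG result would mean. The hypothesis in Objectives {7} is that multi-target stimulation strengthens interactions in the motor-learning network. If any site, band or time point may serve as the primary EEG result, one P value below 0.05 is weak support for that hypothesis, although it would be reported as a primary finding.

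**Working it through.** **1. The plan's own figure.** Sample size {14} gives an effect size of 0.526 from an SRTT study, alpha 0.05, power 0.95 and 32 participants. A noncentral F calculation with three groups reproduces this if two measurements (m = 2) with correlation ρ = 0 are assumed; the article states neither setting. λ = f²·N·m/(1 + (m − 1)ρ) = 0.526² × 32 × 2 = 17.71, with 2 and 29 degrees of freedom, gives power 0.956. Then 32 × 1.2 = 38.4, rounded up to 39, or 13 per arm at 1:1:1. The same sentence also says 10 per group; 13 is used below. The calculation covers one SRTT test at 0.05. It contains no EEG effect, so it implies no EEG variable.

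**2. Definition of outcomes, side by side.**

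| Outcome | Status | Variable fixed in {12} |
|---|---|---|
| Box and Block Test | secondary | blocks moved in 60 s |
| MEP | secondary | average of five traces; latency and amplitude |
| CMCT | secondary | difference of two latencies |
| EEG | primary | none; recording settings only |

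Section {18a} refers back to {12} for the outcome assessment plans, so nothing further is supplied there.

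**3. Size if tests were independent.** The chance of at least one P < 0.05 under no effect is 1 − 0.95^m for m tests.
- 5 bands: 1 − 0.95^5 = 0.226
- 32 channels in one band: 1 − 0.95^32 = 0.806
- 32 × 5 = 160 channel-band pairs: 1 − 0.95^160 = 0.9997, with 160 × 0.05 = 8 false positives expected

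**4. Size with correlated tests.** EEG channels are correlated, so null trials were simulated (at least 3,000 per setting): three arms of 13 and one three-group F test (2 and 36 degrees of freedom) per channel-band pair at 0.05. Two channels in the same band correlate at r_c. The band-level components correlate at r_b, so values in different bands correlate at r_c × r_b. All correlations are assumptions; the article gives none.

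| r_c / r_b | Chance of at least one P < 0.05 |
|---|---|
| 0.5 / 0 | 0.98 |
| 0.5 / 0.3 | 0.97 |
| 0.7 / 0.3 | 0.89 |
| 0.8 / 0.5 | 0.72 |
| 0.9 / 0.7 | 0.48 |
| 0.95 / 0.8 | 0.31 |
| 0.99 / 0.9 (extreme) | 0.15 |

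With one band fixed and all 32 channels open, the chance is about 0.54 at r_c = 0.5 and about 0.19 at r_c = 0.9 (0.13 at 0.95).

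**5. SRTT and EEG as alternative primaries.** If either may succeed at 0.05 and they are independent: 1 − 0.95² = 0.0975. At 0.025 each: 1 − 0.975² = 0.0494.

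**6. Does the MANOVA help?** With 39 patients in three groups there are 39 − 3 = 36 error degrees of freedom, fewer than 160 variables. It cannot be run on all channel-band pairs. Variables must be selected first, and no selection rule is given.

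**The case against.** The strongest objection is that this is a journal article without its analysis plan, and that EEG feature selection is often settled there. That is fair for processing detail such as filtering, artefact handling and epoching. It is not fair for the identity of a primary outcome, which belongs in the protocol. The article gives its clinical and TMS secondary outcomes more definition than this primary one.

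A second objection is that the significance rule is not the only safeguard, since an omnibus multivariate test, a conditional Bonferroni correction and blinded statisticians are all planned. This stands in part: it would be wrong to call the rule wholly uncorrected. But the Bonferroni is tied to post hoc comparisons, the MANOVA needs a prior choice of variables, and a blinded analyst can still pick the variable that separates coded groups.

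A third objection concerns size, and it stands. A reader might infer that a positive primary EEG result is more likely than not by chance alone. The documents do not support that. No section plans to test every channel in every band; the five bands come from a general description in the Background, and 32 is the channel count of the device. Several settings above fall below one half. The simulated test is also a simple three-group comparison, whereas {20a} plans repeated measures.

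**Conclusion.** The point holds in this form: EEG is declared primary, but the article names no EEG measure, band, region or time point. The stated P < 0.05 rule does not govern the choice among EEG variables or the combination of SRTT and EEG. The excess over 5% depends on how many variables are examined and how they correlate. Under single testing of channel-band pairs it is about 0.3 to 0.98 for channel correlations of 0.95 down to 0.5, and 0.15 in the most extreme setting tried. With one band fixed it is about 0.2 to 0.5 for channel correlations of 0.9 down to 0.5. The testing grid and the correlations are assumptions, so these are illustrations of scale, not predictions for this trial. Every setting tried exceeds 0.05, so the conclusion that the nominal level is not secured does not hinge on any one of them.

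**What to change.** In Outcomes {12}, before any unblinded look at the data, do one of the following.

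- **Option A.** Make SRTT the sole primary outcome and move EEG to secondary or exploratory.
- **Option B.** Keep EEG primary and name one variable: the measure; a band near 40 Hz and clear of the 50-Hz notch; the region or connection; and the change from T0 to one stated time point. The sponsor should choose the region or connection to match the network hypothesis. M1 alone fits poorly, because M1 is stimulated in both active arms. Then state in {20a} either that both SRTT and EEG must succeed, or that alpha is split, for example 0.025 each.

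Under either option, label all other EEG measures exploratory and report them with false-discovery or cluster control.

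The cost is a few sentences and no new data. EEG effects elsewhere can then be reported only as exploratory. Splitting alpha slightly lowers power for SRTT: under the settings that reproduce the plan's 32, power at 0.025 instead of 0.05 falls from 0.956 to 0.916 with 32 participants and from 0.984 to 0.967 with 39. Holding power at 0.95 would need 36 participants instead of 32, before dropout. Option A avoids this loss.

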**Fig. 3 Fig3:**
[figure not shown]
EEG will be recorded from the subject while performing the SSRT

Before commencing the experiment, the researcher will brief the participants with the following instructions: (1) ensure minimal movements (except for the hand button movements), especially the head should not sway left or right; (2) refrain from actions such as swallowing and biting while engaging in button pressing; (3) turn off communication devices, such as mobile phones, or set them to silent or in flight mode to mitigate external distractions.

#### Secondary outcomes

##### Box and block test (BBT)

The Box and Block Test (BBT) is a functional test to measure unilateral gross manual dexterity with satisfactory reliability and validity [34], which will serve as the assessment tool to evaluate motor function in stroke patients, including grasping, transporting, and releasing objects. The BBT contains 150 colored wooden cubes, each measuring 1 in. The participants will be tasked with transferring the blocks from one box to another as soon as possible within 60 s, exclusively employing the hemiplegic hand [34]. To facilitate familiarity with the task, participants will be granted a 15-s practice session before the formal assessment commences. Upon the conclusion of the test, the study researcher will count the number of successfully transported blocks. It is important to note that a higher count of transported blocks corresponds to a greater degree of hand function proficiency.

#### Transcranial magnetic stimulation (TMS)

##### Motor-evoked potential (MEP) and central motor conduction time (CMCT)

Single pulse transcranial magnetic stimulation (sTMS, Xiang Yu Medical; China) with a figure-of-eight magnetic coil will be used for measuring motor-evoked potential (MEP) and central motor conduction time (CMCT) [35]. The MEP will be recorded using surface electrodes on the first dorsal interosseous muscle, which is a standard approach for upper limb studies. Participants will be comfortably seated, relaxing their heads and arms. The coil will be placed 5 cm lateral to the vertex along the auricular line (over the M1 of the brain-affected side), aligning at a 45-degree angle from the brain midline, with the handle pointing backwards. The location yielding consistently maximal MEP responses will be identified as the “motor hotspot” [36]. The magnetic stimulus intensity will be set at 20% above the threshold for MEP. The TMS operator will adjust the intensity of the magnetic cortical stimulus to elicit MEPs with a peak-to-peak amplitude of on average 1 mV [37]. Sequential stimulation will be administered five times at each intensity, and the average of the resulting five MEP traces will be used as the outcome for data analysis. Latency will be reported as the mean and standard deviation (SD), while amplitude will be represented by the median due to data distribution skewness.

CMCT denotes the conduction time from the motor cortex to the spinal motor neurons. Spinal magnetic stimulation will be used to measure CMCT. Following the aforementioned cortical stimulation, each participant will undergo cervical stimulation using the coil positioned above the C7 spinous process, situated 2 cm lateral to the midline. The stimulation aims to activate cervical nerve roots at the intervertebral foramina. Participants will encounter an MEP with a latency time attributed to cortical magnetic stimulation of the first dorsal interosseous muscle and find an MEP with another latency time due to cervical magnetic stimulation of the same muscle (peripheral motor conduction time). The difference between the two latency times was the CMCT. They will then experience an MEP characterized by a distinct latency due to cervical magnetic stimulation of the same muscle (representing peripheral motor conduction time). The disparity between these two latency times provides the CMCT value.

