### Eligibility criteria {10}

#### Inclusion criteria

Age between 40 and 75 years, possessing normal or corrected-to-normal vision.Right-handedness, as indicated by a score greater than 40 points on the Edinburgh Handedness Scale [27].Experienced a single (first ever), unilateral stroke (ischemic or intracerebral hemorrhagic) within the timeframe of 2 weeks to 6 months from onset.Exhibiting clear consciousness and absence of mental disorders, with a score exceeding 23 points on the Mini-Mental State Examination (MMSE) [28].Demonstrating a willingness to cooperate in the research and providing voluntary consent by signing the informed consent form.Presenting an upper limb with a Brunnstrom scale grade ranging from III to V.

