#### Exclusion criteria

Presence of contradictions for tACS, TMS, or MRI, such as implantable electronic device or compromised skin in the stimulation area resulting from damage or hyperalgesia.Diagnosis of any other neurological conditions, including depression, severe language comprehension deficits, unilateral spatial neglect, epilepsy, upper-limb apraxia, etc.Proficiency in demanding finger movements, such as piano players, professional game players, and individuals with prior experience in sequential response time testing (SRTT).Ongoing participation in concurrent clinical studies.Identifications of additional reasons, as deemed by researchers, rendering the participant unsuitable for inclusion in the experiment.Inability to comprehend or provide a signature on the informed consent form.

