##### Short intracortical inhibition (SICI) and intracortical facilitation (ICF)

Paired pulse TMS (pTMS, Xiang Yu Medical; China) will be used to measure short intracortical inhibition (SICI) and intracortical facilitation (ICF), both of which are important indicators for evaluating the plasticity of the cerebral cortex. Building upon the preceding procedures, SICI and ICF entail a stimulation at 80% of the resting threshold (RT), a second stimulation at 120% of RT, and an interstimulus interval (ISI) of 3 ms and 12 ms, respectively [38]. Similar to the MEP assessment, each parameter will be subjected to five stimulations to calculate the average value. All the TMS procedures mentioned above will be completed by a professional physiotherapist with 5 years of clinical experience [39].

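### A recordable affected-side MEP is not an entry requirement, and the protocol does not separate a tested-but-absent MEP from missing data, so its carry-forward rule can drop or misstate TMS secondary outcomes

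*Protocol article*

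**What the plan says.** The abstract lists the measures concerned: "The secondary outcomes include motor evoked potential (MEP), central motor conduction time (CMCT), short interval intracortical inhibition (SICI), intracortical facilitation (ICF").

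Among the inclusion criteria, the stroke criterion reads "Experienced a single (first ever), unilateral stroke (ischemic or intracerebral hemorrhagic"), with no limit on lesion site, and the motor criterion reads "Presenting an upper limb with a Brunnstrom scale grade ranging from III to V". The TMS-related exclusion is limited to contraindications: "Presence of contradictions for tACS, TMS, or MRI, such as implantable electronic device". Neither list mentions a recordable MEP.

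In the section on MEP and CMCT, the coil is placed "over the M1 of the brain-affected side". On intensity, "The magnetic stimulus intensity will be set at 20% above the threshold for MEP"; the next sentence has the operator tune the output until the average response is about 1 mV. CMCT is the cortical latency minus the cervical latency. Amplitude is to be summarised by the median because it is skewed. For the paired-pulse measures, "SICI and ICF entail a stimulation at 80% of the resting threshold (RT), a second stimulation at 120% of RT".

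The Statistical methods section {20a} plans a repeated-measures two-way analysis of variance, with a Wilcoxon test where its assumptions fail, under intention to treat. On absent values it says: "In the case of missing data, the last observation value will be used for interpolation". No section says how a test that elicits no response is recorded or scored.

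**The concern.** A stroke that damages M1 or its descending tract can leave no MEP on the affected side. The entry criteria allow such lesions, and grade III patients are expected, because Sequence generation {16a} makes Brunnstrom III, IV and V separate strata. An absent response is then a finding about the patient, not a gap in the data. Carry-forward is built for gaps. Applied to a non-response, it has nothing to work with at baseline, and after a loss it inserts a value for a quantity that no longer exists.

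At stake is the TMS part of the trial's mechanism question. Return or loss of an MEP is a large change in corticospinal response, and it is the change that this handling would leave out. The analysed set would also shrink without any statement of who is in it, although the protocol declares intention to treat.

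**Working it through.** No figure in the protocol is in dispute, so the check sets the sections side by side and then illustrates scale.

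**Step 1. What each measure needs**

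| Measure | Needs | If no MEP can be elicited |
|---|---|---|
| MEP latency | a cortical response | undefined |
| CMCT | cortical minus cervical latency | undefined |
| SICI, ICF | resting threshold (80% and 120% of it) | intensities cannot be set; undefined |
| MEP amplitude | intensity 20% above threshold | that intensity cannot be set, but 0 mV is a meaningful score |

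Amplitude differs from the rest: it can be given a value, although the protocol does not say that it will be.

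**Step 2. What carry-forward does if a non-response is treated as missing**

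- Absent at T0, present later: no earlier value exists, so the T0 cell stays empty. A repeated-measures ANOVA on complete rows drops the patient, and change from baseline cannot be calculated.
- Absent throughout: the patient drops out in the same way.
- Present at T0, absent later: the last measured value is copied forward, so the loss reads as no change. For CMCT, latency, SICI and ICF this enters a number at a visit where the quantity does not exist.
- Present throughout: unaffected.

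The TMS visits cannot be confirmed because the schedule table is not shown. The argument needs only a baseline and one later visit.

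**Step 3. Scale, on assumed rates**

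The protocol gives N = 39 allocated 1:1:1, so 39 / 3 = 13 per arm. It gives no rate of absent MEPs. With an assumed share a, the number affected at T0 is 39 × a in total and 13 × a per arm:

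| Assumed a | Total | Per arm |
|---|---|---|
| 10% | 39 × 0.10 = 3.9 | 13 × 0.10 = 1.3 |
| 25% | 39 × 0.25 = 9.75 | 13 × 0.25 = 3.25 |
| 40% | 39 × 0.40 = 15.6 | 13 × 0.40 = 5.2 |

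**Step 4. How a difference could be hidden (invented counts, mechanism only)**

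Take 13 per arm, 4 per arm without an MEP at T0, a regained MEP worth +0.5 mV, a lost one worth −1.0 mV, and all other patients unchanged.

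- Arm A regains 3 and loses 0. With absence scored as 0, the mean change is (3 × 0.5 − 0 × 1.0) / 13 = 1.5 / 13 = +0.115 mV.
- Arm B regains 1 and loses 2. The mean change is (1 × 0.5 − 2 × 1.0) / 13 = −1.5 / 13 = −0.115 mV.
- Under carry-forward with T0-absent patients dropped, each arm has 13 − 4 = 9 patients and a mean change of 0.

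This shows what the rule can do. It does not estimate what will happen in this trial.

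**The case against.** The strongest reply is that the carry-forward sentence covers missing data and never classes a tested-but-absent MEP as missing. If absence is a result, the rule does not apply, and what remains is a scoring convention that an article may leave to a fuller document. The first part stands: a reader might infer that the protocol prescribes the handling in Step 2, and it does not. The second part answers only some of the concern. The protocol itself fixes entry without an MEP, measures that require one, and a single unqualified rule for absent values. Followed literally, that combination gives wrong values for the latency- and threshold-based measures after a loss.

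Other objections also carry weight:

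- **Frequency.** The reaction-time task needs individual finger presses with the hemiplegic hand, and the Box and Block Test needs grasp and release. These demands, with the exclusion at the researchers' discretion, may make absent MEPs uncommon. They do not rule them out: no minimum performance is set, and none of them is an MEP criterion. Loss of an MEP within two weeks has no stated frequency either.
- **Test used.** Skewed amplitude may go to the Wilcoxon test. If that means a rank-sum comparison at a single visit, regained patients could enter at that visit, though not in a change-from-baseline comparison.
- **Direction.** A reader might infer that the TMS results are biased towards no change in both directions. The documents do not support this. Dropping T0-absent patients also removes those who never show an MEP, which is restriction to a subset and not necessarily bias.
- **Amplitude.** A reader might also infer that all four outcomes cease to exist without an MEP. Amplitude can be scored 0.

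**Conclusion.** The concern holds in a conditional form. Eligibility admits patients in whom latency, CMCT, SICI and ICF cannot be defined and the stated MEP intensity cannot be set, and the protocol does not tell a non-response from a missing test. If non-responses fall under carry-forward, patients without an MEP at T0 leave repeated-measures and change-from-baseline comparisons, and patients who lose the MEP keep an outdated value.

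The size is unknown. The 4, 10 and 16 of 39 rest entirely on the assumed 10%, 25% and 40%. Only secondary mechanistic outcomes are affected; the reaction-time and EEG primary outcomes are not, and these patients still contribute to every non-TMS measure. It is worth correcting because the correction is cheap and is best fixed before the data are analysed.

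**What to change.** In the TMS and statistical methods sections:

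1. Record affected-side MEP status (present or absent) at every TMS visit, and report return and loss by arm.
2. Score a tested-but-absent MEP amplitude as 0 and compare amplitude by rank.
3. Do not apply last-observation fill-in to any TMS measure when the MEP was tested and absent.
4. Report latency, CMCT, SICI and ICF in a declared subset with an MEP at T0, giving its size by arm. State that this subset still leaves out patients who regain an MEP; they are captured only by MEP status and amplitude.
5. Reconcile the two intensity statements (20% above threshold, and tuning to about 1 mV). If the second governs, the operator largely sets the amplitude, and it says little as an outcome whatever the scoring.

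The cost is one yes/no field per TMS visit and a few lines of text, with no extra procedure and no change to entry criteria. The downside is that, where MEPs are absent, latency, CMCT, SICI and ICF are openly reported in fewer than 39 patients.

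### Two unreconciled stimulus-intensity rules govern the same MEP measurement, and amplitude would carry no treatment information if intensity is re-set to 1 mV at each assessment

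*Protocol article*

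**What the plan says.** The abstract of the protocol article lists MEP and CMCT among the secondary outcomes: "The secondary outcomes include motor evoked potential (MEP), central motor conduction time (CMCT". The section *Motor-evoked potential (MEP) and central motor conduction time (CMCT)* then sets out the measurement.

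- Intensity, first statement: "The magnetic stimulus intensity will be set at 20% above the threshold for MEP".
- Intensity, second statement, directly after it: "The TMS operator will adjust the intensity of the magnetic cortical stimulus to elicit MEPs with a peak-to-peak amplitude of on average 1 mV".
- Repetition: "Sequential stimulation will be administered five times at each intensity".
- Analysed quantity: "the average of the resulting five MEP traces will be used as the outcome for data analysis".
- Summary: latency by mean and SD, while "amplitude will be represented by the median due to data distribution skewness".

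The next section, on SICI and ICF, describes the paired-pulse test as "a stimulation at 80% of the resting threshold (RT), a second stimulation at 120% of RT". It contains no 1 mV target.

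The article does not say that either MEP rule serves a separate purpose, that the 1 mV intensity is found once and then kept, or that the adjusted intensity is itself analysed.

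**The concern.** Amplitude is meant to show whether cortical excitability changes. It can do so only if the stimulus is set by something other than the amplitude it produces. Under the 1 mV sentence the operator turns the output up or down until the response reaches a target, and the size of that response is then analysed. If this is repeated at each assessment, a patient who has become more excitable simply receives a weaker pulse. The treatment effect moves into the intensity setting, which the article does not list as an outcome.

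Explaining brain mechanisms, with TMS as one of the tools, is a stated aim of the trial. A flat amplitude comparison produced by titration could be published as evidence that tACS leaves excitability unchanged. If the two rules are used for different patients or visits, amplitude differences may reflect the rule and not the treatment.

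**Working it through.** The plan gives no figure to reproduce here. The check is a comparison of the text, followed by an illustration.

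**1. Can both rules hold at once?** Write A for the mean MEP amplitude, I for the stimulus intensity and T for the threshold.

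- Rule 1: I = 1.2 × T, and A is free.
- Rule 2: I is chosen so that mean A = 1 mV, and I is free.

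They agree only for a patient whose mean amplitude at 1.2 × T happens to be 1 mV. For everyone else they give different intensities.

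**2. Does another part of the article explain the 1 mV sentence?** A natural explanation would be that it sets the test pulse for SICI and ICF. That section instead specifies "a second stimulation at 120% of RT", so the explanation fails.

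**3. What does rule 2 do to a between-arm comparison?** If I is re-set at each assessment, expected amplitude is 1 mV in every arm. The expected difference is 1 − 1 = 0 mV for any true effect.

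**4. Illustration.** Inputs from the article: 39 patients allocated 1:1:1, so 39 / 3 = 13 per group, and five traces averaged per measurement. All other inputs are assumptions, because the article gives none: median amplitude 0.6 mV at 120% of threshold; SDs on the log scale of 0.6 between patients, 0.5 between traces, 0.3 between visits and 0.15 for titration error. Two groups were compared after treatment by a rank-sum test at two-sided 0.05, with 4,000 repetitions. The Monte Carlo standard error near 5% is √(0.05 × 0.95 / 4000) = 0.34 percentage points.

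| True amplitude ratio | Fixed 120% of threshold: observed ratio, rejection | Re-set to 1 mV each time: observed ratio, rejection | 1 mV found at baseline and held: observed ratio, rejection |
|---|---|---|---|
| 1 | 1.01, 4.8% | 1.00, 5.6% | 1.00, 5.2% |
| 1.5 | 1.50, 27.5% | 1.00, 4.8% | 1.50, 66.1% |
| 2 | 2.01, 64.6% | 1.00, 5.2% | 2.00, 97.9% |
| 3 | 3.02, 95.8% | 1.00, 5.1% | 2.98, 100% |

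The re-set column stays at the false-positive rate whatever the true effect. This follows from the titration and not from the assumed SDs. The percentages in the other two columns do depend on those assumptions. The fixed-120% column also assumes that the whole effect appears in amplitude and none in the threshold.

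**The case against.** The strongest reply is that the section never says when, or how often, the operator adjusts to 1 mV. If the setting is found at baseline and then kept, later amplitudes are free to change; in the illustration this reading detects effects more often than the fixed 120% rule. The reference to five stimuli at each intensity hints at more than one condition, and the expected skewness suggests that the authors foresee amplitudes that vary.

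Much of this stands. A reader might infer that the MEP amplitude comparison must be null whatever tACS does. The text permits that reading but does not state it, so the null is conditional on re-setting at each assessment. What does not stand is the idea that the ambiguity is harmless. No list of intensities is given, the outcome is the average of a single set of five traces, and holding the baseline setting is nowhere stated. Because the article prints both rules, this is a contradiction and not a detail left to a fuller document.

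Three other inferences also go too far:

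- **A threshold-based rule would show a true 50% rise as 50%.** This fails if threshold is re-measured at each visit. A fall in threshold lowers the intensity too, so part of the effect is normalised away.
- **The rules might be mixed across sites.** The trial is single-site; the risk lies between patients or visits.
- **Amplitude would be fixed at all of T0 to T3.** Table 1 is not shown in the text available, so the visits at which MEP is measured are not known here.

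**Conclusion.** The intensity specification is wrong as written: two incompatible rules stand together, nothing else in the article reconciles them, and the article does not say whether the setting is held or re-set across visits. If intensity is re-set to 1 mV at each assessment, the expected between-arm amplitude difference is zero and a test rejects at about its nominal 5%. If the 1 mV setting is fixed at baseline, amplitude remains informative.

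The scope is limited. The loss of information concerns amplitude, one component of one secondary mechanistic measure. Latency and CMCT are not pinned by an amplitude target. The primary outcomes, SRTT with EEG, are unaffected. The contradiction itself rests on the text alone; the rejection rates in the illustration rest on assumed amplitude parameters. No view is taken on which intensity is right.

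**What to change.** Reconcile the two sentences into one intensity rule, applied identically at every visit at which MEP is measured. State whether the intensity, or the threshold on which it is based, is fixed at baseline or re-measured. Then match the analysed quantity to the rule:

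- **Intensity not re-titrated to an amplitude target:** amplitude may be analysed as an outcome.
- **Intensity re-titrated to 1 mV at each assessment:** analyse the intensity needed to reach 1 mV in place of amplitude.
- **Intensity set relative to a threshold re-measured at each visit:** analyse resting threshold alongside amplitude, because part of any effect may appear there.

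The cost is about one sentence of protocol text and a little extra analysis, with no added stimuli or visits.
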